# Administrative Responsibilities

This study will be conducted in accordance with Good Clinical Practice, all applicable regulations and the NHMRC National Statement of Ethical Conduct in Human Research.

## **Human Research Ethics Committee (HREC)**

The Clinical Protocol, PICF, and associated documents and any other relevant documentation shall be reviewed and approved by the HREC prior to participant enrolment. All proposed changes, including administrative changes, to the protocol, PICF, associated documents and other relevant documentation must be reviewed and approved by the HREC prior to implementation.

Investigators are responsible for obtaining and maintaining annual renewal of the study by their HREC.

## **Informed Consent Procedures**

Informed consent is a process that is initiated prior to the individual’s agreeing to participate in the study and continues throughout the individual’s study participation. Participant Information and Consent forms (PICF) must be approved by the HREC and Research Governance Office at each site. Participants will be asked to read and review the document. An interpreter will be provided as per NSW Health Policy for any participant who is not fluent in English. The investigator will explain the study to the participant and answer any questions that may arise. A verbal explanation will be provided in terms suited to the participant’s comprehension of the purposes, procedures, and potential risks of the study and of their rights as research participants. Participants will have the opportunity to carefully review the written consent form and ask questions prior to signing. The participants should have the opportunity to discuss the study with their family or surrogates or think about it prior to agreeing to participate.

The participant will sign the informed consent document prior to any procedures being done specifically for the study. Participants must be informed that participation is voluntary and that they may withdraw from the study at any time, without prejudice. A copy of the informed consent document will be given to the participants for their records. The informed consent process will be conducted and documented in the source document (including the date), and the form signed, before the participant undergoes any study-specific procedures. The rights and welfare of the participants will be protected by emphasizing to them that the quality of their medical care will not be adversely affected if they decline to participate in this study.

All participants will provide informed consent prior to the PCI procedure.

## **Confidentiality**

All data collected concerning participants or their participation in this study will be considered confidential. All information collected about participants for the study will have the participant's name and address removed so that they cannot be recognised by it. The information will instead be labelled with a code. The Investigator (or delegate) is responsible for keeping a code list which makes it possible to link a participants assigned code to their name, so that in case of an emergency they can be identified and contacted. The Investigator will keep this code list in a secure location to protect participant privacy. The code list will be kept for the period required by applicable regulations and guidelines (a minimum of 15 years) or as per the institutions procedures. Each investigator must assure that the privacy of the participants, including their personal identity and all personal medical information, will be maintained at all times. In eCRFs and other documents participants will be identified not by their names, but by an identification code e.g. identification number. Personal medical information may be reviewed for the purpose of verifying data recorded on the eCRF. This review may be conducted by the trial monitor, properly authorised persons on behalf of South Western Sydney Local Health District. Personal medical information will always be treated as confidential.

All data used in the analysis and reporting of this evaluation will be used in a manner without identifiable reference to the participant.

## **Study Registration and Publication Policy**

Registration of this study is on the Australian New Zealand Clinical Trials Registry.

Results of the study will not be actively disseminated to participants, however, once the study results are available and have been published, participants will be given the opportunity to receive them upon request via the investigator. The Investigator is responsible for sharing these results with the participant as agreed by the participant. In addition, a summary of the results will be available on http://www.anzctr.org.au/

# APPENDIX A. DEFINITIONS

*MACE Definitions*

**Major Adverse Cardiac Event (MACE):** MACE is defined as cardiac death, Q-wave or non Q-wave myocardial infarction (MI), or clinically driven target vessel revascularization (TVR) by percutaneous or surgical methods.

**Cardiac Death:** Death due to cardiac causes. If the cause of death cannot be determined, it will be categorized as cardiac.

Myocardial Infarction (Protocol Definition):

Clinically relevant MI after coronary revascularization is defined as:

- Participants with normal baseline cardiac biomarkers
  - CK-MB >10x ULN or cTn (I or T) >70x ULN, or
  - CK-MB >5x ULN or cTn >35x ULN plus new Q-waves in >2 contiguous leads or LBBB
- Participants with elevated baseline cardiac biomarkers
  - Baseline biomarkers are stable or falling:
    - CK-MB >10x ULN or cTn (I or T) >70x ULN of **most recent pre-procedure level**, or
    - CK-MB >5x ULN or cTn >35x ULN of **most recent pre-procedure level** plus new Q-waves in >2 contiguous leads or LBBB
- Baseline biomarkers have not been shown to be stable or falling: CK-MB (or cTn) rises by an absolute increment equal to those recommended above plus new ST-segment elevation or depression plus signs consistent with a clinically relevant MI, such as new onset or worsening heart failure or sustained hypotension.

**Target Vessel Revascularization (TVR):** Ischemia-driven repeat percutaneous intervention of the target vessel or bypass surgery of the target vessel. A TVR will be considered as ischemia-driven if the target vessel diameter stenosis is
[figure not shown]
≥50% and any of the following are present:

- A positive functional study corresponding to the area served by the target vessel.
- Ischemic ECG changes at rest in a distribution consistent with the target vessel.
- Ischemic symptoms referable to the target lesion.

**In-Hospital MACE:** MACE that occurs within 72 hours of the procedure or prior to hospital discharge, whichever occurs first, in a participant treated with the CorPath GRX System.

*Other Definitions*

**Adverse Event Classification**

An adverse event is defined as any adverse change in health or undesirable clinical occurrence from the participant’s baseline whether it is considered device related or not.

An adverse event is considered serious if it results in death, is life-threatening, requires hospitalization or prolongation of existing hospitalization, results in persistent or significant disability/incapacity or is an important medical event which may jeopardize the participant and may require medical or surgical intervention to prevent one of the above outcomes.

**Procedure-Related Adverse Event**

An adverse event is procedure-related when, in the judgment of the Investigator, it is reasonable to believe that the event is not associated with the CorPath GRX System use. Instead, other products, surgical techniques, or medications required specifically for the procedure are deemed by Investigator as likely to have contributed to the occurrence of the event.

**Abrupt Closure:** The occurrence of new severely reduced flow (TIMI flow grade 0 or I) within the target vessel that persisted and required rescue by a non-assigned treatment strategy (including emergency surgery), or resulted in MI or death. Abrupt closure requires proven association with a mechanical dissection of the treatment site or instrumented vessel, coronary thrombus or severe spasm. Abrupt closure does not connote “no reflow” (due to microvasculature limitation), in which the epicardial artery is patent but had reduced flow. Abrupt closure also does not connote transient closure with reduced flow in which the index treatment application reversed the closure.

**Coronary Dissection** - Refers to a split or a tear in the wall of the [artery](http://www.wikidoc.org/index.php/Artery) which compresses or compromises the [lumen](http://www.wikidoc.org/index.php/Lumen) of the [artery](http://www.wikidoc.org/index.php/Artery) reducing blood flow.

**Coronary Guidewire Dissection** - A coronary dissection where a coronary guidewire is inadvertently positioned in a subintimal position or when stiff-tipped or hydrophilic-tipped guidewires are used to cross highly stenosed or totally occluded arteries.

**Coronary Perforation** - Coronary perforation occurs when a dissection or intimal tear propagates outward sufficient to completely penetrate the arterial wall. This may be caused by pre/post balloon dilatation or post stent deployment where the stent edge causes an edge perforation. Stent edge perforation will range in severity. Ellis classification of coronary perforation:

- Type I - Focal extraluminal crater without extravasation
- Type II - Pericardial or myocardial ‘blush’ without contrast agent
- Type III - Contrast agent ‘jetting’ through a frank (>1 mm) perforation

**Access Site Complication:** A complication occurring at the access site that requires either local intervention or blood transfusion.

**Subacute Thrombosis:** An abrupt closure of the target vessel that occurs after the index procedure is completed (and the participant has left the catheterization laboratory) and within 24 hours of the PCI.

**Threatened Abrupt Closure:** A grade B dissection and >50% diameter stenosis or any dissection of grade C or higher.

**Bleeding Requiring Transfusion:** Any blood loss requiring transfusion of blood products. Transfusion without clinical evidence of bleeding will be recorded separately.

**Coronary Artery Bypass Graft Surgery (CABG):** Classified as emergent, urgent, or elective as follows:

- **Elective**: the participant is clinically stable and the overall medical condition does not indicate the need for revascularization within forty-eight (48) hours.
- **Urgent**: the participant is clinically unstable and the condition warrants revascularization within two (2) to forty-eight (48) hours.
- **Emergent**: the participant is clinically unstable and the condition requires immediate revascularization within two (2) hours.

**Cardiogenic Shock:** Participant presents with systolic blood pressure <80 mm Hg for more than thirty (30) minutes unresponsive to fluids or requiring intravenous pressures or an intra-aortic balloon pump.

**CK:** Creatine kinase, or creatine phosphokinase.

**CK-MB:** An iso-enzyme of creatine phosphokinase (CK) with a distinct molecular structure specific as an indicator of myocardial cell injury. It is used to evaluate possible causes of chest pain, to detect and diagnose acute MI and re-infarction, and to monitor the severity of myocardial ischemia.

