# Study Design

## **Overview**

This is a randomized controlled trial of the CorPath GRX System versus standard PCI to compare participant outcomes at 72 hours post-procedure or hospital discharge, day 30 and 1 year.

The study population will consist of all consecutive participants undergoing PCI at Liverpool Hospital being asked to provide written informed consent prior to PCI and meet the eligibility criteria.

The study will randomize 300 participants equally into the 2 arms:

- Arm 1: PCI using the CorPath GRX System
- Arm 2: PCI using standard care

All enrolled participants will be followed post procedure through hospital discharge or 72 hours, whichever occurs first. The follow up will occur at day 30 and 1 year post-procedure

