# Study Intervention Discontinuation and Participant Discontinuation/ Withdrawal

In the event that the participant is randomized but does not go ahead to have PCI or there is a requirement to move from technology-assisted PCI to manual PCI they will not be discontinued from the study and the remaining study procedures should be completed as indicated by the study protocol. Any discontinuation of the participant after the PCI is described in Section 6.1.

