### Conversion to Manual Procedure Data Collection

The Investigator shall determine if it is necessary to convert to standard manual percutaneous techniques to complete the PCI. The Investigator should make this decision based on his/her medical assessment of the situation in accordance with the best interest of the participant. It is recommended that conversion to manual operation be performed at the discretion of the Investigator or if any of the following occur:

- The inability to navigate the guidewire or balloon/stent catheters using the CorPath GRX System as intended.
- Any clinical condition that requires rapid medical intervention.

The reason for conversion to manual should be reported by the operator and documented.

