**Vascular Injuries:**

- **Dissection:** A tear in a vessel allowing blood to enter the wall of the vessel and split its layers. The result is either an intramural hematoma or aneurysmal dilatation.

Dissection classification per National Heart, Lung and Blood Institute:

- Type A: Radiolucent areas within the coronary lumen during contrast injection, with minimal or no persistence of contrast after dye has cleared.
- Type B: Parallel tracts or double lumen separated by a radiolucent area during contrast injection, with minimal or no persistence after dye has cleared.
- Type C: Contrast outside the coronary lumen, with persistence of contrast in the area after dye has cleared.
- Type D: Spiral luminal filling defects frequently with extensive contrast staining of the vessel.
- Type E: New persistent filling defects that may be caused by thrombus.
- Type F: Non type A-E dissection types that lead to impaired flow or total occlusion of the coronary artery.

**No Reflow:** Defined as a sustained or transient reduction in antegrade flow that is not associated with an obstructive lesion at the treatment site.

**Perforation:** Perforations are classified as follows:

- **Angiographic** **perforation**: Perforation detected by the clinical site at any point during the procedure.
- **Clinical** **perforation**: Perforation requires additional treatment beyond IV fluid administration (including efforts to seal the perforation or pericardial drainage), or resulting in significant pericardial effusion, abrupt closure, myocardial infarction, or death.

**Restenotic Lesion:** Defined as lesion in a vessel that had undergone a prior percutaneous treatment.

**Thrombus:** Discrete, mobile intraluminal filling defect with defined borders with or without staining.

Thrombosis: Academic research Consortium (ARC) definitions:

- **Definite stent thrombosis** requiring the presence of an acute coronary syndrome with angiographic or autopsy evidence of thrombus or occlusion**.**
- **Probable stent thrombosis** includes unexplained deaths within 30 days after the procedure or acute myocardial infarction involving the target-vessel territory without angiographic confirmation.
- **Possible stent thrombosis** includes all unexplained deaths occurring at least 30 days after the procedure.

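### The Appendix A definition of abrupt closure depends on the allocated arm, so any by-arm count of it is tilted against the CorPath device

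*Protocol*

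**What the plan says.** Protocol Appendix A, under Procedure-Related Adverse Event, defines abrupt closure as new TIMI 0 or I flow in the target vessel that "persisted and required rescue by a non-assigned treatment strategy (including emergency surgery), or resulted in MI or death". The same entry excludes "transient closure with reduced flow in which the index treatment application reversed the closure". It does not say what a non-assigned strategy is.

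Section 3.1 gives the two assignments as "Arm 1: PCI using the CorPath GRX System" and "Arm 2: PCI using standard care". Section 7.2.6 lists, among the grounds for recommending conversion to manual operation, "Any clinical condition that requires rapid medical intervention". Section 6.0 keeps converted participants in the trial: if "there is a requirement to move from technology-assisted PCI to manual PCI they will not be discontinued from the study".

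Two other Appendix A terms use the definition. Subacute thrombosis is "An abrupt closure of the target vessel that occurs after the index procedure is completed", within a time limit. Clinical perforation covers perforations needing treatment beyond IV fluids, "or resulting in significant pericardial effusion, abrupt closure, myocardial infarction, or death".

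**The concern.** An outcome definition used to compare two arms should classify the same clinical course in the same way in both. This one refers to the assigned strategy, and manual PCI is non-assigned in one arm and assigned in the other. Two participants with the same closure and the same manual rescue could be classified differently because of allocation alone.

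Comparative safety is part of the primary objective (Section 2.1). Adverse events are recorded at the index procedure (Sections 3.3 and 7.2.3), and device- or procedure-related events are monitored in every participant (Section 7.7.1). Appendix A lists abrupt closure among procedure-related events, so a table of procedural complications by arm could well include it. Such a table would show an excess in the CorPath arm even if the true closure risk were equal.

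**Working it through.** **Step 1: apply the definition to each course of a persistent closure.**

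| Course of a persistent TIMI 0/I closure | CorPath arm | Standard arm |
|---|---|---|
| Emergency surgery, MI or death | counted | counted |
| Rescued by manual PCI, none of these | counted | not counted |
| Rescued robotically, none of these | not counted | does not arise |

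Only the second row differs by arm. Section 7.2.6 makes that row plausible in the CorPath arm, since a persistent closure may well be a condition needing rapid intervention. In the standard arm, the exclusion for closures reversed by the index treatment points the same way.

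**Step 2: see which measures use the term.** Abrupt closure appears only in Appendix A. It is not a component of MACE (Sections 2.2.1 and 7.7.2, Appendix A), clinical success (2.2.1) or technical success (2.3). Section 2.4 names MACE and SAEs as the safety measures, and Section 7.7.2 limits the serious events reported to those meeting MACE.

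**Step 3: illustrate the size.** The protocol gives no figure for abrupt closure to reproduce. Its one power statement (Section 8.1) concerns patient radiation dose. The only input taken from the document is 150 participants per arm; the rest is assumed:

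- p, the true risk of a persistent closure, equal in both arms: 2%, 3% or 5%.
- s, the share of those closures rescued by catheter without surgery, MI or death: 25%, 50% or 75%.
- m, the share of CorPath-arm catheter rescues done by hand: 1 in the main case.

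Expected counted events are:

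- CorPath: 150 × p × [(1 − s) + s × m], which is 150 × p when m = 1.
- Standard: 150 × p × (1 − s).
- Ratio when m = 1: 1/(1 − s).

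The last column is the exact probability that a two-sided Fisher test at 5% is significant with 150 per arm.

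| p | s | CorPath events | Standard events | Ratio | Fisher significant |
|---|---|---|---|---|---|
| 2% | 25% | 3.0 | 2.25 | 1.3 | 1.3% |
| 2% | 50% | 3.0 | 1.5 | 2.0 | 2.2% |
| 2% | 75% | 3.0 | 0.75 | 4.0 | 4.3% |
| 3% | 50% | 4.5 | 2.25 | 2.0 | 5.5% |
| 3% | 75% | 4.5 | 1.13 | 4.0 | 13.0% |
| 5% | 25% | 7.5 | 5.63 | 1.3 | 4.2% |
| 5% | 50% | 7.5 | 3.75 | 2.0 | 11.9% |
| 5% | 75% | 7.5 | 1.88 | 4.0 | 32.9% |

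With one definition in both arms, the Fisher probability is 1.2%, 1.9% and 2.4% at p = 2%, 3% and 5%.

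If only half of the CorPath-arm catheter rescues are manual (m = 0.5), the ratio is (1 − s/2)/(1 − s): 1.17, 1.5 and 2.5 for s = 25%, 50% and 75%.

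**Step 4: check the dependent terms.** Subacute thrombosis carries the same rescue criterion, but less is at stake. It arises after the participant has left the laboratory, so the conversion rule in Section 7.2.6 does not govern its rescue. A repeat intervention can also count as target vessel revascularisation, on the same terms in both arms. Clinical perforation is barely affected: its limb for treatment beyond IV fluids would ordinarily capture a perforation needing catheter rescue, whichever arm it occurs in.

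**The case against.** The strongest objection is that nothing planned depends on the term. Section 8.1 applies Fisher's test to secondary outcomes, and abrupt closure is never listed as one. This stands, and it limits the point to counts of abrupt closure and of terms built on it. Section 8.1 does leave room for analyses beyond those listed, and the event is of a kind the trial collects, so a by-arm table remains possible.

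A second objection is that *strategy* may mean PCI as against surgery, which would make the definition neutral. The protocol calls its arms methods of PCI and calls the switch a conversion. The reading is possible but is not the plain one: surgery is given as something included in the class, so the class is wider than surgery, and the only thing assigned in this trial is robotic or standard PCI. If both readings are open, event reviewers may classify the same case differently, which also calls for a change of wording.

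A third objection is that the size rests on assumed rates and on every CorPath-arm catheter rescue being manual. This stands in full. Robotic rescue shrinks the ratio, and the 33% figure is the extreme corner of the grid.

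**Conclusion.** On its plain wording the definition depends on the arm, always in the direction of more counted events with CorPath. Under the stated assumptions the ratio at equal true risk is 1.3 to 4.0, falling to 1.17 to 2.5 if half of the CorPath-arm catheter rescues are manual. At a 2% risk a false significant test is unlikely (1.3% to 4.3%), and it becomes material only when closures are common and mostly rescued by catheter. The practical harm is a lopsided descriptive count.

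A reader might infer that the trial's main safety comparison is biased against the device. The protocol does not support that: abrupt closure is outside MACE, its surgery, MI and death limbs work alike in both arms, and no test of it is planned. Nor does the document support a claim that a false finding of harm is likely, since it gives neither a closure rate nor a rescue share.

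**What to change.** In Appendix A, replace the reference to a non-assigned strategy with one event-classification criterion that does not mention allocation. Two forms would serve:

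- Count a persistent closure that needed bail-out treatment of any kind (manual, robotic or surgical) or resulted in MI or death.
- Count a persistent closure only if it was rescued by a strategy other than PCI, or resulted in MI or death.

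Either gives an expected ratio of 1.0 at equal true risk. The first counts more events and needs a clear definition of bail-out, so that it neither lowers the severity bar unintentionally nor clashes with the transient-closure exclusion. The second keeps the bar high and yields fewer events. The investigators should choose before any data are compared by arm.

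Word the exclusion for closures reversed by the index treatment so that it reads the same in both arms. State that conversion to manual operation is recorded separately, as Sections 2.6, 7.2.3 and 7.2.6 already require, and does not by itself make an event. Subacute thrombosis and clinical perforation then follow without further editing.

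The cost is a short change to Appendix A and to the eCRF guidance. It affects only how events are classified, not how participants are managed. The small downside is that counts become less comparable with reports using the strategy-based definition.
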